## Abstract

**Introduction:**

Current evidence suggests the emergence of a novel syndrome (long COVID syndrome) due to sequels and persistent COVID-19 symptoms. Respiratory muscle training improves respiratory muscle strength, exercise capacity, diaphragm thickness, and dyspnea, especially in patients with decreased respiratory muscle strength. This study aims to evaluate the effectiveness of a protocol for home-based inspiratory muscle training to improve respiratory muscle strength, dyspnea, and quality of life of patients post-COVID-19.

**Methods and analyses:**

This randomized, controlled, double-blind clinical trial will be conducted at the Instituto de Medicina Tropical of Universidade Federal do Rio Grande do Norte (Brazil). Sample size will be determined using maximal inspiratory pressure after a pilot study with five patients per group (total of 10 patients). Patients included in the study will be evaluated in three moments: pre-training (initial), post-training (three weeks), and retention (24 weeks). The sample will be randomized in two groups: active (IMT using 30% of IMT and load increase of 10% of initial IMT every week. Patients will perform 30 repetitions, twice a day (morning and afternoon), for seven consecutive days, and six weeks) and SHAM (IMT without load). The following measurements will be assessed: anthropometry, respiratory muscle strength, pulmonary volume and capacity, dyspnea, perception of effort and lower limb fatigue, handgrip strength, functional capacity, anxiety, depression, and functional status. After initial evaluation, all patients will receive a POWERbreathe® (POWERbreathe®, HaB Ltd, Southam, UK) device to perform the training. Normality will be verified using Shapiro-Wilk or Kolmogorov-Smirnov, according to the number of patients included. Variables presenting nonparametric distribution will be compared using Wilcoxon (intragroup analysis) and Mann-Whitney test (intergroup analysis), whereas repeated measures two-way ANOVA will be performed in case of parametric distribution. Dunn’s post hoc test will be used to identify significant differences in the two-way ANOVA test.

**Primary outcomes:**

Respiratory muscle strength, dyspnea, and quality of life of post-COVID-19 patients.

**Second outcomes:**

Pulmonary function, dyspnea, exercise tolerance, handgrip strength, anxiety, depression, and functional status.

**Trial registration:**

Trial register number NCT05077241.

## Introduction

Researchers estimated that 81% of confirmed COVID-19 cases are mild, with mean recovery time of two weeks; 14% progress to severe pneumonia and 5% to severe acute respiratory syndrome, sepsis, and multiple organ failure [1]. Older adults are more affected and present 8% to 15% lethality [2].

Lungs are the most affected organ. Cough, sputum production, and shortness of breath are the most common symptoms after fever [3]. Extrapulmonary manifestations (e.g., cardiovascular, gastrointestinal, neurological, hepatic, renal, cutaneous, and hematological) also contribute to complications after the acute phase of the disease [4].

Evaluation of patients 60 days after onset of first symptoms showed that only 12.6% were free of COVID-19 symptoms, 32% presented one or two symptoms, and 55% three or more symptoms. Worse quality of life was observed in 44.1% of patients. Fatigue (53.1%), dyspnea (43.4%), joint pain (27.3%), and chest pain (21.7%) were also reported. Carfi et al. (2020) [5] highlighted that 87.4% of patients post-COVID-19 reported persistence of at least one symptom, mainly fatigue and dyspnea.

Six to twenty percent of post-COVID-19 patients present mild to moderate muscle weakness after 6 to 8 weeks of hospital discharge. Approximately one-third presented persistent pulmonary function impairment after one year of follow-up. Health status of COVID-19 survivors was worse than the non-infected population. Abnormal chest radiography, persistent reduction of exercise capacity, and impaired musculoskeletal performance and quality of life were also reported [6].

Dyspnea is one of the main respiratory symptoms after COVID-19 and may be associated with reduced respiratory muscle strength. Performance of respiratory muscles might be affected by several factors: aging, obesity, sedentary behavior, smoking, and chronic diseases. The increased load to respiratory muscles in patients with chronic pulmonary disease is due to reduced respiratory muscle strength and changes in airway resistance and chest wall mechanics. Long-term pulmonary impairments (e.g., fibrotic interstitial lung disease) might also be developed after the disease and may be associated with chronic inflammation caused by COVID-19 [6]. Thus, patients infected may present imbalance between respiratory muscle strength and respiratory demand, increasing the risk of respiratory failure [7].

Viral respiratory diseases are also associated with acute and long-term psychopathological consequences [8]. Patients post-COVID-19 may present delirium, anxiety, depression, and insomnia. These symptoms are induced by sequels of viral infection in the central nervous system or indirectly through immune response [9]. Mazza et al. (2020) [10] investigated psychiatric symptoms of 402 post-COVID-19 patients and demonstrated signs of post-traumatic stress disorder (28%), depression (31%), anxiety (42%), obsessive-compulsive disorder (20%), and insomnia (40%). This study also observed that systemic immune-inflammation index of patients was positively associated with depression and anxiety. Therefore, psychopathology of patients who survived COVID-19 must be assessed to diagnose and treat emergent psychiatric conditions [11].

A pilot study carried out with 42 participants recovered from covid-19 after mechanical ventilation, with a two-week IMT protocol (2x a day, 5x a week, 6 inspiratory cycles with each cycle for 5 minutes interspersed with 60 seconds of rest) improves function pulmonary function (FVC and FEV1), dyspnea, functional performance (6MWT) and QoL [12].

Another study involving 281 participants in the post-covid period, with an 8-week IMT program (3x week, up to 6 times of 6 inspirations with the rest periods interspersed with each inspiration progressively decreasing from 40 to 10 s with each block, producing durations 20-min session maximums) showed significant improvements in the intervention group for the “shortness of breath and activity” and “psychological” subdomains of the KBILD quality of life questionnaire. Greater reduction in dyspnea was also observed, improvement in inspiratory muscle strength, increase in functional capacity and levels of physical activity [13].

## Objectives

### Primary objective

This study aimed to evaluate the effectiveness of a home-based inspiratory muscle training (IMT) protocol compared to an IMT SHAM group for improving respiratory muscle strength, dyspnea, and quality of life of post-COVID-19 patients.

### Secondary objective

To evaluate the influence of IMT on pulmonary function, perception of effort, dyspnea, exercise tolerance, handgrip strength, anxiety, depression, and functional status.

## Material and methods

### Type of study and location of research

This randomized, controlled, double-blind, parallel, two arm clinical trial will be conducted at the Instituto de Medicina Tropical and of Universidade Federal do Rio Grande do Norte, referred from the ambulatory of infectology of Hospital Giselda Trigueiro (Rio Grande do Norte, Brazil) will be recruited.

Sample size will be determined using maximal inspiratory pressure (MIP) (GPower Software version 3.1.9.2, Kiel, Germany) after a pilot study with five patients in each group (total of 10 patients). Mean and standard deviation will be used to estimate effect size, and a bilateral distribution with alpha error of 0.05 and 80% power will be adopted. Sample size will be adjusted assuming a dropout rate of 20%.

### Inclusion criteria

Sedentary patients of both genders, diagnosed with COVID-19 using reverse transcription polymerase chain reaction, aged above 18 years, without other respiratory diseases associated or cardiac disease, with adequate cognitive capacity (Mini-Mental State Examination [MMSE]), and reduced respiratory muscle strength will be included. Reduced inspiratory muscle strength will be defined using MIP [14].

### Exclusion criteria

Patients with conditions impairing assessments, health complications that justify interrupting data collection (e.g., syncope, intense chest pain, or cough with blood-tinged sputum), hospitalized due to exacerbation of clinical conditions, or requested to leave the study will be excluded.

Regarding recruitment, researchers will contact the Hospital Giselda Trigueiro and inform patients about the study.

The sample will be randomized (www.randomization.com) in two groups: active (AG, IMT with load) and SHAM (SG, placebo IMT without load). Groups will be coded, and allocation will be included in sealed and opaque envelopes numbered consecutively.

This study will include three investigators: the first will be responsible for assessments; the second, adjustment of training load; and the third, randomization. This is a double-blinded study because the first researcher and patients will be blinded to allocation of patients and intervention effects.

This protocol was approved by the research ethics committee of Universidade Federal do Rio Grande do Norte (Brazil) (CAAE**:** 45575421.7.0000.5537) on May 1, 2021 and submitted to Clinical Trials (NCT05077241). Autonomy and anonymity of patients will be respected, ensuring personal data privacy according to resolution nº 510/16 of the National Health Council and Declaration of Helsinki. Before entering the study, all patients will sign the informed consent form.

Our study was written in accordance with Standard Protocol Items: Recommendations for Interventional Trials (SPIRIT), which was aim to improve the quality of clinical trial (S1 Checklist).

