### Interventions

Patients included will be evaluated in three moments: pre-training (initial), post-training (six weeks after pre-training), and retention (24 weeks after pre-training). After recruitment, one researcher previously trained and blinded to allocation will evaluate vital signs, anthropometric measurements, pulmonary volume, respiratory muscle strength, handgrip strength, quality of life, anxiety, depression, functional status, and functional capacity.

After initial evaluation, all patients will receive a POWERbreathe® (POWERbreathe®, HaB Ltd, Southam, UK) device and be individually oriented on how to perform the IMT protocol. An experimental session will be conducted for familiarization with the device. Patients will receive a phone call every three days from the second researcher (who will not participate in the evaluation) to confirm if IMT is being performed correctly and resolve doubts regarding the protocol. At the end of each week, patients from EG will receive a video call from the second researcher to adjust load of the device.

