#### Adverse effects and adherence

Adverse effects and adherence will be assessed using a training diary will be given to all patients to assess adverse effects and adherence. After all training sessions, they will be encouraged to fill the diary, registering positive and negative observations and complications during and after training. Adherence will be assessed considering every time patients register the realization of the session. Fulfilled sessions will be added and then divided by the total number of sessions patients could perform.

Adherence to training will be considered by verifying the number of days that patients performed the sessions. The sum of all sessions performed will be divided by the total number of sessions that patients must perform. Adverse effects will consider all complications registered in the diary or mentioned during final evaluations.

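### The exclusion criteria include events that can happen after randomisation; if excluded means lost to follow-up or analysis, the comparison can be biased and a serious event can go unrecorded

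*Protocol article*

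**What the plan says.** The Exclusion criteria section of the Protocol article names, among the reasons for exclusion, "health complications that justify interrupting data collection (e.g., syncope, intense chest pain, or cough with blood-tinged sputum" and patients "hospitalized due to exacerbation of clinical conditions, or requested to leave the study will be excluded". It gives no time point for these events and does not say what the patient is excluded from. The next paragraphs of the same section describe recruitment and then allocation: "The sample will be randomized (www.randomization.com) in two groups".

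Assessments after baseline are fixed under Interventions: "post-training (six weeks after pre-training), and retention (24 weeks after pre-training". The sample size is still to be derived "after a pilot study with five patients in each group (total of 10 patients", with "a bilateral distribution with alpha error of 0.05 and 80% power will be adopted". Attrition appears once, in the section on type of study and location: "Sample size will be adjusted assuming a dropout rate of 20" per cent.

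On safety, the section on adverse effects and adherence says: "Adverse effects will consider all complications registered in the diary or mentioned during final evaluations". All patients receive the diary and are encouraged to complete it after each session. Under Interventions, all patients are also telephoned every three days, but the stated purpose is to check performance of the training and resolve doubts.

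**The concern.** Eligibility criteria should describe a patient before allocation. Here they are mixed with events that belong to the course of the trial. Nobody can ask to leave a study before joining it, and data collection cannot be interrupted before it starts. With six weeks of training and follow-up to week 24, much of the time at risk for these events lies after randomisation.

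The arms may differ in how often such events occur. One arm trains against a load that rises each week, while the other has no load. Only the active arm has the weekly load-adjustment video call. Complications, withdrawals and retention could each therefore depend on the arm. They could also be related to inspiratory pressure, dyspnea and quality of life, which the trial is designed to compare. If such patients leave follow-up or analysis, the difference between those who remain mixes the effect of training with the effect of selection.

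The same patients matter most for safety. Someone hospitalised and then excluded may stop the diary and never attend a final evaluation. In that case neither named source captures the event.

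**Working it through.** **No figure of the plan can be reproduced.** The article gives no sample size, SD or exclusion count. The figures below are illustrations on assumed values. Only the 20% dropout, the two-sided 0.05 level and the 80% power come from the article.

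**Step 1: when each criterion can act.**

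- Request to leave: only after entry, and at any time up to week 24.
- Complications interrupting data collection: at the baseline tests, or at any later assessment.
- Hospitalisation for exacerbation: at screening or later.
- Conditions impairing assessments (also listed): reads naturally as a screening criterion.

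**Step 2: extreme selection, no true effect.** Suppose the worst fraction p of a normal outcome is removed. The mean of those who remain rises by L(p) = φ(z)/(1 − p) SD, where z cuts off a tail of p.

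- L(0.05) = 0.1031/0.95 = 0.109
- L(0.10) = 0.1755/0.90 = 0.195
- L(0.15) = 0.2332/0.85 = 0.274
- L(0.20) = 0.2800/0.80 = 0.350

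Spurious differences between arms:

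- 15% vs 5%: 0.166 SD
- 20% vs 10%: 0.155 SD
- 10% vs 5%: 0.086 SD

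**Step 3: moderate selection, no true effect.** Let the tendency to be excluded have correlation r with a poor outcome, with r = 0.3 or 0.5 (assumed). The bias is r × [L(f) − L(g)] for excluded fractions f (active) and g (sham). The splits below average 20% if the arms are of equal size, to match the plan's overall dropout. L(0.25) = 0.3178/0.75 = 0.424 and L(0.30) = 0.3477/0.70 = 0.497.

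For the type I error, the variance of retained outcomes is v = 1 − r² + r²(1 − zL − L²). The standard error is SE = √[v_f/(n(1 − f)) + v_g/(n(1 − g))]. With b = bias/SE, the error is Φ(−1.96 − b) + 1 − Φ(1.96 − b).

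Example for 30% vs 10%, r = 0.5, n = 79 per arm: bias = 0.5 × (0.497 − 0.195) = 0.151; SE = √(0.873/55.3 + 0.928/71.1) = 0.170; b = 0.89; type I error = 14.4%.

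| Excluded, active vs sham | r | Bias (SD) | Type I error, n = 25 / 32 / 79 randomised per arm |
|---|---|---|---|
| 20% vs 20% | 0.3 or 0.5 | 0 | 5.0% / 5.0% / 5.0% |
| 25% vs 15% | 0.3 | 0.045 | 5.2% / 5.3% / 5.8% |
| 25% vs 15% | 0.5 | 0.075 | 5.7% / 5.9% / 7.3% |
| 30% vs 10% | 0.3 | 0.091 | 6.0% / 6.2% / 8.1% |
| 30% vs 10% | 0.5 | 0.151 | 7.9% / 8.7% / 14.4% |

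**Step 4: what the 20% inflation does.** At two-sided 0.05 and 80% power, assumed standardised effects of 0.5, 0.8 and 1.0 need 63, 25 and 16 per arm. Dividing by 0.8 gives 79, 32 and 20. This restores the number analysed. It leaves the bias unchanged and shrinks the SE, so the type I error rises with n in every unequal row of the table.

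**Step 5: safety sources.** The two named sources are the diary and the final evaluation. Diary entries made before exclusion still count. An event that leads to exclusion and is neither written down nor followed by a final visit has no named route into the data.

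**The case against.** The strongest reply is that the section never says these patients leave the analysis. Excluded may mean only that they discontinue, and the plan already allows for dropout. The timing is also open. The baseline visit includes maximal pressure manoeuvres, spirometry and a walk test, so syncope or chest pain could interrupt data collection there. The article does not fix whether randomisation comes before or after that visit. Hospitalisation can be a screening criterion. An article may leave the analysis population and the handling of missing data to the full protocol or analysis plan.

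Much of this stands. A reader might infer that the plan breaks the randomised comparison, but removal from analysis is nowhere stated, so the comparison is put at risk rather than shown to be broken. A reader might also infer that the most serious safety events are discarded. The text does not support that: all complications in the diary count, and no sentence drops the events of excluded patients. The missing intention-to-treat sentence is not the point either.

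What does not stand is that the wording is harmless. It is a stated rule, and part of it can act after randomisation. Nothing in the article keeps such patients in follow-up or analysis. The repeated-measures ANOVA and Wilcoxon tests named under Statistical analysis, as conventionally run, use only patients with the required visits.

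**Conclusion.** The concern holds in conditional form. The Exclusion criteria section mixes eligibility with events that can follow randomisation, and it leaves open what exclusion means. If it means removal from follow-up or analysis, the result can be biased by about 0.05 to 0.15 SD under the assumed moderate selection and by about 0.17 SD in the assumed extreme case of 15% vs 5%. The latter figure belongs to that split and is not a ceiling for every split. The bias is zero if exclusion is equal in both arms by the same mechanism. The exclusion rates, their split by arm and the correlations with outcome are assumptions. The plan's 20% is overall dropout and implies no difference between arms.

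On safety, the conclusion is narrower than a loss of events by design: a serious event in an excluded patient could go unrecorded. Because selection cannot be undone once follow-up is lost, the wording should be settled before patients are dropped under it.

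**What to change.** 1. Limit the exclusion criteria to conditions present before randomisation.
2. State that patients with later complications, hospitalisation or withdrawal stay in follow-up at six and 24 weeks as far as they consent, and are analysed in their allocated group.
3. Report complications and hospitalisations by arm for all randomised patients, including those who discontinue. Record them also at the three-day calls already made to both groups, with the same fixed questions in each arm because the caller also adjusts the load.

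Whether training stops after such an event is a clinical matter for the sponsor and is not prescribed here.

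The cost is a change of wording, a short checklist on existing calls and somewhat more follow-up work. The estimated effect may be smaller than one based on retained patients alone.

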### Interventions

Patients included will be evaluated in three moments: pre-training (initial), post-training (six weeks after pre-training), and retention (24 weeks after pre-training). After recruitment, one researcher previously trained and blinded to allocation will evaluate vital signs, anthropometric measurements, pulmonary volume, respiratory muscle strength, handgrip strength, quality of life, anxiety, depression, functional status, and functional capacity.

After initial evaluation, all patients will receive a POWERbreathe® (POWERbreathe®, HaB Ltd, Southam, UK) device and be individually oriented on how to perform the IMT protocol. An experimental session will be conducted for familiarization with the device. Patients will receive a phone call every three days from the second researcher (who will not participate in the evaluation) to confirm if IMT is being performed correctly and resolve doubts regarding the protocol. At the end of each week, patients from EG will receive a video call from the second researcher to adjust load of the device.

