#### Dyspnea

Dyspnea will be assessed using the Medical Research Council scale adapted to Portuguese. Patients must indicate the impact of dyspnea on mobility during daily activities. Scores range between 1 and 5, and highest values indicate greater dyspnea [17].

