#### Intervention protocol

The following training protocols will be applied.

Active group protocol: IMT using 30% of MIP and load increase of 10% of initial MIP every week. Patients will perform 30 repetitions, twice a day (morning and afternoon), for seven consecutive days, and six weeks. Patients will be instructed to perform a fast inspiratory muscle contraction, sustain it for two seconds, and expire. Thirty seconds of rest will be allowed every three IMT repetitions to avoid muscle fatigue or complications.

Sham group protocol: patients will use an IMT device without load and receive the same instructions as EG. If the treatment applied to EG be effective, we will invite patients from CG at the end of the study to perform the IMT protocol with load.

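### The weekly video call to adjust the load goes to the active group only; it can reveal allocation to patients and makes contact unequal, while two primary outcomes are self-reported

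*Protocol article*

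**What the plan says.** The Interventions section of the protocol article describes two kinds of remote contact during training.

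- The first goes to patients in general: "Patients will receive a phone call every three days from the second researcher". Its purpose is to check technique and answer questions.
- The second is limited to one arm: "At the end of each week, patients from EG will receive a video call from the second researcher to adjust load of the device".

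The abbreviation EG is not defined. The randomization paragraph (under Exclusion criteria) calls the arms AG and SG. The Intervention protocol section settles the meaning: if the treatment given to EG works, the other group will be offered training with load. EG is therefore the active arm.

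The active regimen is "IMT using 30% of MIP and load increase of 10% of initial MIP every week", performed "twice a day (morning and afternoon), for seven consecutive days, and six weeks". In the sham arm, "patients will use an IMT device without load and receive the same instructions as EG". No weekly video call and no mock adjustment is described for sham patients.

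On blinding, the article states: "This is a double-blinded study because the first researcher and patients will be blinded to allocation of patients and intervention effects".

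The primary outcomes are "Respiratory muscle strength, dyspnea, and quality of life of post-COVID-19 patients". For dyspnea, measured with the MRC scale, "Patients must indicate the impact of dyspnea on mobility during daily activities". Quality of life is measured with the SF-36 questionnaire.

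**The concern.** The blinding claim rests on patients not knowing their arm, yet the plan gives one arm a recurring procedure that the patient sees and the other arm lacks. A patient whose device is adjusted on video every week has a cue pointing to active training. A patient who is never adjusted may have a cue pointing to sham. The cue repeats throughout six weeks.

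A second problem does not depend on anyone guessing. The active arm has an extra type of supervised contact with the second researcher. This may influence technique, adherence (which patients record themselves in a diary) and how patients feel. The estimated effect then combines loaded training with additional attention.

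Two of the three primary outcomes are the patient's own reports, and a blinded assessor cannot protect those from expectation or attention. Because the extra contact coincides completely with arm, the planned Mann-Whitney tests or two-way ANOVA cannot separate it from the effect of load. It has to be dealt with in the design.

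**Working it through.** The article gives no figure for contacts per arm and no sample size, effect size or SD, so there is nothing of its own to reproduce. The check is a comparison of the sections, a count of contacts, and an illustration under assumed values.

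**1. What each arm receives**

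| Element | Active | Sham |
|---|---|---|
| Phone call every three days | yes | yes |
| End-of-week video call | yes | not described |
| Weekly change of device setting | yes | none described; no load |
| Patient said to be blinded | yes | yes |

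As written, the active setting over weeks 1 to 6 runs 30%, 40%, 50%, 60%, 70%, 80% of initial MIP (30 + 10 × number of completed weeks). Each change coincides with a video call.

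**2. Planned contacts**

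Inputs: six weeks of training and a phone call every three days. There are five or six end-of-week video calls, depending on whether one is made after the last week, when no training week remains to adjust for.

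- Duration: 6 × 7 = 42 days.
- Phone calls, each arm: 42 / 3 = 14.
- Active arm, if video calls are additional: 14 + 5 = 19 or 14 + 6 = 20.
- Excess over sham: 5/14 = 36% or 6/14 = 43%.

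The article does not say whether the video calls are additional. If only calls falling on the same day are merged (days 21 and 42 are multiples of both 3 and 7), the active total is 14 + 6 − 2 = 18 with six video calls, or 14 + 5 − 1 = 18 with five. The excess is then 4/14 = 29%. If every video call replaces a phone call, both arms have 14 contacts and the excess in number is zero. The active arm would still be the only one with video contact and load adjustment.

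**3. What a reporting bias could do (assumed values only)**

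Suppose the true effect on a self-reported outcome is zero and the lack of blinding or unequal attention shifts the group difference by *b* SD. With *n* per arm, the shift in the test statistic is *s* = *b* / √(2/*n*). The two-sided 5% test then rejects with probability 1 − Φ(1.96 − *s*) + Φ(−1.96 − *s*). The values of *n* are those giving 80% power for assumed standardized effects of 0.8 and 0.5.

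| *n* per arm | *b* = 0.2 | *b* = 0.3 |
|---|---|---|
| 25 (effect 0.8) | *s* = 0.71, 11% | *s* = 1.06, 19% |
| 63 (effect 0.5) | *s* = 1.12, 20% | *s* = 1.68, 39% |

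These rates show how sensitive the test is to a modest bias. They do not estimate the bias in this trial.

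**The case against.** The strongest reply is that the call does not by itself disclose the arm. Patients train at home, and someone who gets no weekly adjustment can infer sham only by knowing that the other arm gets one. The article does not say that patients are told this. That stands: the call can reveal allocation, and the documents do not show that it will.

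Three further inferences that a reader might draw are not supported.

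- **That the call contradicts the sham description.** The statement that sham patients get the instructions given to EG most naturally refers to the breathing technique described just before it. That can be identical in both arms whoever is called to adjust the device. The tension is with the blinding statement.
- **That every outcome is biased towards active.** MIP, the variable chosen for the sample size, is measured by an assessor blinded to allocation, from at least three reproducible maneuvers. It needs maximal effort, so it is not immune, but it is clearly less exposed than the MRC scale or SF-36. The six-minute walk is also effort-dependent, but exercise tolerance is a secondary outcome.
- **That the active arm certainly has 36% to 43% more contact.** This holds only if the video calls are additional to the phone calls.

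It can also be said that a matched call would not restore blinding fully, because an unloaded device may feel different and a mock adjustment may be noticed. That is fair, and it limits what the remedy can promise. It does not justify leaving an avoidable cue in place.

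The condensed format of an article is no answer here. It explains missing detail, whereas this text expressly assigns the call to one arm.

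**Conclusion.** The point holds in this form: the article assigns the weekly load-adjustment video call to the active arm alone and describes nothing equivalent for sham. This undercuts the statement that patients are blinded and leaves supervised contact unequal in kind. In number, the imbalance is about 19 to 20 against 14 contacts over 42 days if the video calls are additional, and anything down to none if they are combined with the phone calls.

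The main exposure is in MRC dyspnea and SF-36, with less in MIP. The direction most to be feared favours the active arm, but the size of any bias cannot be derived from the document. Confidence is high on the asymmetry itself and lower on how many patients would infer their arm. Since the analysis cannot undo the problem after data collection, it should be corrected in the plan.

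**What to change.** In the Interventions section, state that patients in both groups receive the end-of-week video call from the second researcher, with the same script and the same length. In the sham group the call includes a mock adjustment that leaves the assigned condition unchanged; how to carry it out convincingly is for the investigators to decide. Use the arm labels from the randomization paragraph throughout.

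State also how the video calls relate to the three-day phone calls. One planned phone call per week can become the video call in both arms, which keeps the total at about 14 each. If the video calls are additional, the total is 19 to 20 in each arm.

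The cost is a script and a few minutes per sham patient per week from the researcher who already makes the calls. No new staff or visits are needed, and the active regimen is untouched.

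This equalises attention and removes the cue from the call. It does not remove any cue from the feel of an unloaded device. As an option, ask each patient at the post-training visit which group they think they were in, and report the answers by arm. Read them with caution, since perceived benefit can influence the guess.
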